## Scope of the analysis

This document outlines the plan for the primary analysis of the results of the SEHER: Strengthening evidence-base on school-based health promotion interventions trial for the primary SEHER results publication.

Some descriptive and follow-on analyses that will not be included in the primary paper have also been included in this protocol.

# 1 Description of the trial

See SEHER trial protocol (Annexure A).

## 1.1 Principal research objectives to be addressed

Primary objectives

1. To assess the effectiveness of the SEHER intervention plus Tarang-Adolescence Education Programme (AEP) delivered by the Teacher as SEHER *Mitra* (TSM) compared to AEP alone in building school climate as measured with Beyond Blue School Climate Questionnaire (BBSCQ) at 8 months.

2. To assess the effectiveness of the SEHER intervention plus AEP delivered by the SEHER *Mitra* (SM) compared to AEP alone in building school climate as measured with BBSCQ at 8 months.

Secondary objectives

3. To assess the effectiveness of the SEHER intervention plus AEP delivered by the SM compared to SEHER intervention plus AEP delivered by the TSM in building school climate as measured with BBSCQ at 8 months.

Sensitivity analysis will be performed for objectives 1, 2 and, 3 with those participants who have completed BOTH the base and end-line assessment.

4. Objectives # 1, 2 and, 3 will be analysed stratified by gender.

5. To assess the effectiveness of the i) SEHER intervention plus AEP delivered by the TSM compared to AEP alone; ii) SEHER intervention plus AEP delivered by the SM compared to AEP alone, and iii) SEHER intervention plus AEP delivered by the SM compared to SEHER intervention plus AEP delivered by the TSM in:

1. Improving attitudes towards gender equity as measured with adapted version of Gender Equitable Men Survey
2. Increasing knowledge and attitudes towards reproductive and sexual health (RSH) as measured with adapted version of WHO’s Illustrative Questionnaire for Interview with Young People
3. Reducing depression as measured with Patient Health Questionnaire-9 (PHQ-9)
4. Reducing self-reported experience of bullying behaviour as measured with adapted version of Illinois Bullying Scale
5. Reducing self-reported violence (perpetration and victimisation) as measured with adapted version of Global School-based student Health Survey (GSHS)

6. Objective # 5 will be analysed stratified by gender.

7. To measure the costs and cost effectiveness of the TSM and SM interventions in improving the school climate scores compared to the AEP alone.

Objective # 5 will also be tested for exploratory outcomes (listed below). For these behavioural outcomes the trial does not have enough power to detect anything except extremely large differences between the intervention and comparison arms as being statistically significant due to the low prevalence of these behaviours at baseline. However, we perceive that it is important to gather information on these behavioural measures and to measure and report the results by trial arm.

a) Incidence of self- reported suicide behaviour during 8 months

b) Incidence of self-reported tobacco use (smoking and chewing) during 8 months

c) Incidence of self-reported alcohol use during 8 months

d) Incidence of self-reported other substance use during 8 months

e) Incidence of self-reported initiation of sex during 8 months

f) Incidence of self-reported forced sexual encounters during 8 months

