| Knowledge of and attitude towards RSH | Questionnaire on knowledge and attitude of towards RSH | 8 items questionnaire; minimum and maximum score range between 0 and 8 with higher scores indicating better knowledge of and attitude towards RSH |
| Depression | Patient Health Questionnaire-9 | 9 items; minimum and maximum scores range between 0 and 27 with higher scores indicating severe depression; recall period: last 2 weeks |
| Exploratory Outcome | | |
| Substance use | GSHS | 14, items measure use of tobacco (chewing and smoking), alcohol and other substances in last 8 months (since the class IX started) and last 30 days, frequency of use in last 30 days |
| Sexual behaviour | GSHS | 4 items measure sexual behaviour, and experience of forced sex in last 8 months (since the class IX started) |
| Suicide attempts | GSHS | One item measures suicide attempt in last 8 months (since the class IX started) |

Process indicators

The coverage of each component, the quality of intervention implementation (fidelity), and the extent to which stakeholders engaged with it will be examined. Coverage indicators are collected through monthly reporting forms and quality indicators are assessed through ratings of specific components, such as the wall magazine and peer group meetings by respective supervisors, and the observations made by the intervention team during field visits. The stakeholder engagement will be examined through students’ reporting of self-coverage of intervention at the follow-up assessment.

Whole school level activities

- Number of awareness meetings held with students against planned per month
- Number of awareness meetings held with teachers against planned per month
- Number of wall magazines produced against planned per month
- Types of topics covered through wall magazine
- Number of questions addressed against questions received per month through speak-out box
- Types of questions received through speak-out box per month
- Reasons for not addressing certain issues
- Type of competitions organised against planned per month
- Number of students participated in each competition
- Number of School Health Promotion Committee meetings held against planned
- Number of health policies generated and implemented in the school

Group school level activities

- Number of peer groups formed per school
- Number of peer group meetings conducted against planned per month
- Number and types of issues addressed in peer group meetings

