## 1.5 Brief description of proposed analyses

Analyses will be carried out by the Trial Manager ([name]) in collaboration with [name] at LSHTM. Analyses will follow CONSORT guidelines for cluster-randomised trials. The primary analysis data will be analysed under intention-to-treat assumptions (i.e. analyse all those with data from three arms irrespective of intervention received).

Analyses will be conducted in Stata version 14. Do-files will be prepared based on blinded data, and data will not be unblinded until the dataset is finalized, locked and sent to the DSMB chair.

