### *3.1.1 Analysis of primary outcome*

The estimation of the SMD of the total score on the BBSCQ at 8 months between i) the TSM and comparison arm; ii) SM and comparison arm, and iii) the SM and TSM arm will address research objective #1, 2, and 3 respectively, see Section 1.1:

Data will be analysed at individual-level using an intention-to-treat (ITT) analysis, using a linear mixed effects model with outcome of the BBSCQ total score at 8 months with intervention arm as a covariate, and adjusting for the school-level BBSCQ score at baseline. A random effect will be included to account for clustering at school level [2-3].

Sensitivity analyses for participants who have completed both baseline and follow-up assessment (cohort analyses): Independent ANCOVA-type analysis for sample of students who have completed both base and end-line assessment, using a linear mixed effects model with outcome of BBSCQ total score at 8 months with intervention arm as a covariate and adjusting for the BBSCQ total score at baseline and school. A random effect will be included to account for clustering at school level.

The data of the students who have completed base and end-line assessment will be matched through the unique identity number given to each participant.

For gender segregated sample for the participants who have completed end-line assessment: Independent ANCOVA-type analysis for sample of only boys and girls, using a linear mixed effects model with outcome of BBSCQ total score at 8 months with intervention arm as a covariate and adjusting for the school-level BBSCQ score at baseline. A random effect will be included to account for clustering at school level.

Model assumptions of normally distributed data, and the missing at random assumption, will be tested (see section 3.1.3) and if necessary, the outcome analyses will be adapted as appropriate.

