## 3.2 Exploratory analyses

The following are all follow-on analysis.

The models may be extended to include possible predictors of outcome including intervention coverage and students’ self-reporting of coverage.

Inclusion of TSM and SM characteristics in models will be considered.

Any analysis of sub-scales or domains will also be reported as exploratory.

Analysis procedure described in 3.1.1 will be followed for the exploratory outcomes (listed in 1.10.

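### Exploratory outcomes (b) to (e) are defined as incidence or initiation, but the plan sets no at-risk group: the analysis in 3.2 yields period prevalence, and the survival analysis in 3.1.2 conflicts with it and is undefined

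*SAP*

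**What the plan says.** **Target.** SAP section 1.1 lists six exploratory outcomes, each as incidence over 8 months. Item (b) is "Incidence of self-reported tobacco use (smoking and chewing) during 8 months"; (c) and (d) follow the same form for alcohol and other substances; (e) is "Incidence of self-reported initiation of sex during 8 months". The same section explains the lack of power as "due to the low prevalence of these behaviours at baseline", so some students are expected to engage already when the trial starts.

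**Route one.** Section 3.2 states: "Analysis procedure described in 3.1.1 will be followed for the exploratory outcomes". In section 3.1.1 the main model is fitted to individuals at 8 months, "adjusting for the school-level BBSCQ score at baseline". Section 1.5 gives the analysis set: "analyse all those with data from three arms irrespective of intervention received". Students seen twice enter under a separate label: "Sensitivity analyses for participants who have completed both baseline and follow-up assessment (cohort analyses". That model adjusts for the individual baseline score.

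**Route two.** Section 3.1.2, which covers objectives 5 and 6, assigns the onset of self-reported behaviours to survival analysis. Section 1.1 says objective 5 will also be tested for the exploratory outcomes, so this sentence reaches them too.

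**Measurement.** Section 1.4 gives two assessments, with the exploratory outcomes measured at both. Table 1 describes substance use over the last 8 months and the last 30 days. For sexual behaviour it says: "4 items measure sexual behaviour, and experience of forced sex in last 8 months (since the class IX started".

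**The concern.** Incidence and initiation need a denominator of students free of the behaviour at the start and a numerator of those who then take it up. Neither route supplies this. Under 3.2, a student who used tobacco before the trial and still does counts the same as one who began during it.

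A class IX programme might prevent uptake without changing established use, or the reverse. A period-prevalence contrast mixes the two. If the programme acts on uptake only, continuing users in both arms pull the ratio towards 1. If continuing users are unevenly spread across arms at baseline, that imbalance enters a result labelled as new cases. The mislabelling would pass into any publication reporting the incidence of substance use or sexual initiation by arm.

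**Working it through.** **1. Reproduce the flow-chart figures (SAP section 2.1, Figure 1).** Arms are identified by class IX enrolment; the arm with 6447 enrolled and 24 clusters is TSM.

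| Enrolled | Baseline completed | End-line completed | Analysed |
|---|---|---|---|
| 7601 | 4465 (58.74%) | 4623 (60.82%) | 4623 |
| 7502 | 4525 (60.32%) | 5316 (70.86%) | 5316 |
| 6447 | 4046 (62.76%) | 4475 (69.41%) | 4475 |

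The percentages are completed/enrolled and agree with those printed to within 0.1 point. Analysed equals end-line completers in every arm, so no at-risk restriction and no requirement for a baseline record has been applied.

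**2. Analysed students with no baseline record.** The minimum, end-line minus baseline, assumes that every baseline participant returned:

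- 4623 − 4465 = 158; 158/4623 = 3.4%
- 5316 − 4525 = 791; 791/5316 = 14.9%
- 4475 − 4046 = 429; 429/4475 = 9.6%
- Total 1378/14414 = 9.6%

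The maximum, enrolment minus baseline completers with enrolment taken as fixed, is 3136 + 2977 + 2401 = 8514, and 8514/14414 = 59.1%. The number matched is not given, so the true share lies somewhere between. For these students, baseline data cannot establish risk status.

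**3. Compare target and method.**

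| Requirement for incidence of (b) to (e) | 3.1.1 main model | 3.1.1 cohort model | 3.1.2 survival |
|---|---|---|---|
| Baseline record for each student | No, school-level score only | Yes | Not stated |
| Baseline-positive students excluded | No | No, only adjusted for | Not stated |
| Time origin and event time | Not needed for a proportion | Not needed for a proportion | Needed, not defined |

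Table 1 describes no date of, or age at, first occurrence. On that description, two assessments can show whether a behaviour was newly reported between them, but not when it began.

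**4. Direction of the effect, illustration only.** None of these rates is in the SAP. Let p be baseline prevalence, r the share of prevalent cases reporting again at end-line, and i the 8-month incidence among those free of the behaviour. End-line period prevalence is p·r + (1 − p)·i. Assume i = 2% in the comparison arm and 1% in an intervention arm (true ratio 0.50), with no effect on prevalent cases.

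- p = 1%, r = 0.5: 0.0248 against 0.0149, ratio 0.60; prevalent cases are 20% of comparison-arm positives.
- p = 3%, r = 1: 0.0494 against 0.0397, ratio 0.80; prevalent cases 61%.
- p = 10%, r = 1: 0.118 against 0.109, ratio 0.92; prevalent cases 85%.

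Under these assumptions the movement is always towards 1. Its size depends entirely on p and r.

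**The case against.** **The plan does address onset.** A reader who saw only 3.2 might infer that the SAP contains nothing but a period-prevalence analysis. That goes too far: 3.1.2 plans a survival analysis of onset, which presupposes a risk set. The sentence confirms that onset is the target. It does not cure the gap, because nothing needed to run the analysis is defined and 3.2 prescribes something else.

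**A matched cohort already exists.** It would also be wrong to say that individual baseline data are ignored. The procedure in 3.1.1 includes a cohort model with individual baseline adjustment. This stands, and it narrows what is missing to the exclusion of baseline-positive students. Adjusting for prior use still leaves continuing users in both numerator and denominator.

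**The six outcomes differ.** Extending the criticism to all of them is tempting but unsupported. A suicide attempt (a) or a forced sexual encounter (f) is an event, and the proportion with an event in an 8-month window is itself an incidence proportion. Excluding earlier cases of (f) would discard repeat victimisation. For (b) to (d), if any use in the window is what is meant, the fault lies in the word incidence.

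**The items are not shown.** Table 1 is a summary. The end-line survey may have asked about first sex or first use, and the baseline wording is unknown: a window running from the start of class IX fits the March/April 2016 survey, not one completed in July 2015. So it cannot be claimed that the questionnaire is unable to separate new from continuing behaviour, only that the SAP describes nothing that would.

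**Selection.** Restricting to students seen twice adds selection on attendance, and end-line completion already ranges from 60.8% to 70.8% across arms. This is a fair reason to keep the all-attendee comparison alongside.

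**Conclusion.** The concern holds for outcomes (b) to (e). Followed as written, 3.2 with 3.1.1 gives 8-month period prevalence under the name of incidence, and 3.1.2 gives a second, incompatible instruction that cannot be carried out from what the SAP describes. This rests on Table 1 describing the items accurately; a first-occurrence item, if one exists, would change the position and should be stated.

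What is firm is the minimum share of analysed students without a baseline record: 3.4%, 14.9% and 9.6% by arm, unequal between arms. It measures missing baseline information, not how many continuing users are counted. A reader might take the ratios of 0.60 to 0.92 as the expected bias; they rest on assumed rates and on no effect among continuing users, and the SAP supplies neither.

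The primary and secondary score outcomes are untouched. Because the affected outcomes are declared exploratory and underpowered, the change should be made, but it does not threaten the trial's main conclusions.

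**What to change.** Reconcile sections 1.1, 3.1.1, 3.1.2 and 3.2 so that each exploratory outcome has one target, one population and one method.

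- For (b) to (e), keep the comparison of all end-line attendees and label it 8-month period prevalence.
- For (b) to (e), define incidence or initiation in the ID-matched cohort, restricted for each outcome to students not reporting that behaviour at baseline. Use random-effects logistic regression with school as the random effect. Delete the survival sentence in 3.1.2 for these outcomes unless onset dates were collected; if they were, define the risk set, time origin and event time.
- State what the baseline item covers (lifetime or a recall window), so that the meaning of newly reported is clear.
- For (a) and (f), report the proportion with an event in the recall window, without excluding earlier events.
- Report, by arm, the numbers matched and at risk for each outcome.

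**Cost.** The change needs new SAP wording and one restricted run for each outcome (b) to (e). Baseline exploratory measures and the ID match are already planned, so no new data are needed. The restricted analysis has fewer events and is selected on attending both surveys, so it should be shown beside the all-attendee result, with both marked exploratory.

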## 1.2 Trial design including blinding

SEHER is a cluster-randomised controlled trial (CRT) comparing clusters (schools) in: (i) Teacher-as SEHER *Mitra* (TSM) and ii) SEHER *Mitra* (SM) arms versus the control arm (Tarang-Adolescence Education Programme) with follow up over 8 months.

The trial is conducted in 74 schools (24 in TSM arm, 25 in SM arm and 25 in comparison arm) across 20 blocks of Nalanda district of Bihar. All the students studying in class IX in the academic year 2015-16 are invited to participate in the study at each school. In the SEHER *Mitra* arm the SEHER intervention is delivered by a trained lay worker called as SEHER *Mitra*; in the teacher-as SEHER *Mitra* arm, the SEHER intervention is delivered by a trained teacher called a Teacher-as SEHER *Mitra*.

The Tarang- Adolescence Education programme is delivered in all three arms by the nodal teachers selected and trained by the Department of Education with technical assistance from Centre for Catalysing Change, India.

The random allocation of the schools has been carried out by an independent statistician who is not involved in the Trial.

Outcome measures are administered by researchers independent of the intervention and blind to the allocation of the intervention.

The data analyst will be blinded to the clusters’ allocation.

- 1. **Method of allocation of schools**

Of the 136 total of secondary and higher secondary schools in Nalanda, 112 schools that were eligible for inclusion in the trial were identified based on the following criteria:

- Current implementation of Tarang- AEP
- Total number of students in grade IX in a school >100
- Total number of employed teachers in a school >/=4

Of the 112 schools, 75 were randomly selected for the random allocation. To have a representative pool of 75 schools, and to ensure an equal number of schools of each type in each of the three trial arms, we selected 68% of co-educational (63 out of 93), 69% of only girls’ (9 out of 13) and 50% only boys’ schools (3 out of 6). All the 75 schools are allocated to comparison or one of the intervention arms by using minimisation. To carry out the allocation by minimisation [1], the arms were balanced on the following variables (classifying each of the variables into categories):

1. Type of school (secondary=1; and secondary and higher secondary school=2);
2. School size (small=101-300 students in school; medium=301-600, and large=601 and above students ), and
3. Nature of school (Co-education=1; only boys’=2; and only girls’=3).

The random allocation by using minimization was carried out by an independent statistician ([name], LSHTM) using the R software package.

- 1. **Sample size estimation**

The sample size estimations are based on for the changes in the primary and a secondary outcome measure, *viz.* school climate and being bullied, for the total as well gender segregated sample. The average score for school climate and the prevalence of being bullied is drawn from the data collected during the pilot testing of the SEHER outcome assessment questionnaire. The assumptions are:

- The arithmetic mean score on Beyond Blue School Climate scale is 20.6 (SD 6.7) with an ICC of 0.018.
- 18% students in secondary school in Nalanda, Bihar reported experiencing bullying in the last 30 days (were made fun of with sexual jokes, comments, or gestures) with an ICC of 0.03.
- The cluster number is 24 in TSM, 25 each in SM and comparison arm and average cluster size is 115 (60 boys and 55 girls).
- Assumed 15% loss to follow-up.

Based on these assumptions, the proposed trial will have 98% power to detect an effect size of 0.2 (difference in means/SD) school climate score between the comparison and each intervention arm respectively, with 95% confidence and an ICC of 0.02 (88% and 93% power among boys & girls, respectively). The trial will have 83% power to detect a 6% absolute difference in the proportion of students who reported experiencing bullying between the comparison and each intervention arm respectively, with 95% confidence and an ICC of 0.03 (82% and 83% power to detect a 7% and 6% difference among boys and girls, respectively).

- 1. **Duration of the intervention period**

In each intervention arm school (SM and TSM), the SEHER intervention activities were conducted between July 2015 and February 2016. The SEHER intervention activities were delivered at three levels viz. whole-school, group and individual level.

Whole school level activities: Awareness generation, wall-magazine, speak-out box, intra school competitions, healthy school policies, and School Health Promotion Committee.

Group level activities: Peer groups of class IX students, and workshops for class IX students and for all teachers.

Individual level activities: Counselling and referral services for all the students in the school.

These activities were conducted all through the 8 months.

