## 1.4 Data collection

The data were collected at two points; baseline and end-line assessment at 8 month from baseline.

The baseline assessment was completed in July 2015 and the end-line assessment in March/April 2016.

Inclusion criteria

- All the students enrolled and studying in class IX
- Present in the school on the day of assessment

Exclusion criteria

- None

Following data is collected from consented participants: (through contact information form)

Complete name (will not be part of the questionnaire and linked directly with the outcome assessment questionnaire)

Complete address and contact details, if available (will not be reported)

- Class, section, and roll number
- Age (in years)
- Gender
- Caste
- Marital status
- Father’s education
- Mother’s education
- Father’s occupation
- Mother’s occupation
- Baseline measures of the primary, secondary and exploratory outcomes (listed below)

Outcome Measures

The primary outcome measure is overall school climate. The secondary outcome measures are attitudes towards gender equity, knowledge of and attitude towards reproductive and sexual health, experience of bullying, violence, and depression. In addition, the following exploratory^^[[1]](#footnote-2)^^ outcome measures will also be assessed: tobacco, alcohol and other substance use, sexual behaviour, and suicide attempts. The outcome assessment measures are summarised in Table 1.

Table 1: SEHER Trial outcome assessment measures

| Outcome Indicator | Instrument | Description |
| --- | --- | --- |
| Primary Outcome | | |
| School climate | Beyond Blue School Climate Questionnaire (BBSCQ) | 28 items questionnaire; minimum and maximum score range between 0 and 28 with higher scores indicating a more favourable experience of School Climate |
| Secondary Outcome | | |
| Experience of bullying | Illinois Bullying Scale | 4 items questionnaire; score ranges between 0 and 12 with higher scores indicate experience of severe bullying; recall period: last 30 days |
| Violence (perpetration and victimisation) | Global School-based student Health Survey (GSHS) | 4 items; 2 items each on perpetration and experience of physical violence; recall period: last 8 months (since the class IX started) |
| Attitude towards gender equity | Gender Equitable Men Survey | 10 items questionnaire; minimum and maximum score range between 0 and 10 with higher scores indicating more positive attitude towards gender equity |

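### The girls' bullying power (83%) and the boys' school climate power (88%) do not follow from the stated sample size inputs, and the bullying power is for one yes/no item, not the 0–12 score in Table 1

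*SAP*

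**What the plan says.** The sample size text in SAP section 1.2 lists its assumptions and then presents all the powers as based on them.

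- Schools and students: "The cluster number is 24 in TSM, 25 each in SM and comparison arm and average cluster size is 115 (60 boys and 55 girls").
- Attrition: "Assumed 15% loss to follow-up".
- School climate: "The arithmetic mean score on Beyond Blue School Climate scale is 20.6 (SD 6.7) with an ICC of 0.018". The power statement uses an ICC of 0.02.
- Bullying: "18% students in secondary school in Nalanda, Bihar reported experiencing bullying in the last 30 days (were made fun of with sexual jokes"). The ICC assumed here is 0.03, and the figure refers to this one item only.

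The climate powers for 0.2 SD are 98% overall, 88% in boys and 93% in girls. For bullying, "The trial will have 83% power to detect a 6% absolute difference in the proportion of students who reported experiencing bullying" in the whole sample, and by sex "82% and 83% power to detect a 7% and 6% difference among boys and girls, respectively". No prevalence, SD, ICC or number of schools is given separately for boys and girls.

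Table 1 in section 1.4 describes the bullying outcome as "4 items questionnaire; score ranges between 0 and 12 with higher scores indicate experience of severe bullying". Objectives 4 and 6 ask for results stratified by gender, and section 3.1.1 delivers this as "Independent ANCOVA-type analysis for sample of only boys and girls".

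**The concern.** Two inconsistencies show before any calculation.

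- Girls are 55 of the 115 students per school, yet they are given the same 83% power as the whole sample for the same 6-point difference at the same ICC. With one prevalence and the same schools, less than half the cluster size cannot give equal power.
- Boys have more students per school than girls (60 against 55), yet their climate power is lower (88% against 93%) for the same effect, ICC and stated number of schools.

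Either the figures are wrong or they rest on inputs that the SAP does not show. In both cases a reader cannot verify the stated sensitivity of the gender-stratified analyses. The endpoint raises a related problem: a power for a proportion on one item says nothing direct about a four-item score.

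**Working it through.** **Inputs** (SAP section 1.2). 25 v 24 schools, the less favourable intervention-versus-comparison contrast. Cluster size after 15% loss: 0.85 × 115 = 97.75; boys 0.85 × 60 = 51; girls 0.85 × 55 = 46.75. Two-sided 5%, taken from the stated 95% confidence. Bullying is taken as a fall from 18%, to 12% for 6 points or 11% for 7 points.

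**Formulas.** Design effect DE = 1 + (m − 1) × ICC. Effective size per arm n = schools × m / DE. Climate, in SD units: SE = √(1/n₁ + 1/n₂). Bullying: SE = √(p₁(1 − p₁)/n₁ + p₂(1 − p₂)/n₂). Power = Φ(difference/SE − 1.96). A pooled variance under the null lowers the bullying powers by less than half a point; both versions are shown.

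**Whole sample, to check the method.**
- Climate: DE = 1 + 96.75 × 0.02 = 2.935; n = 832.6 and 799.3; SE = 0.0495; 0.2/SE = 4.04; power 98.1% (stated 98%).
- Bullying: DE = 1 + 96.75 × 0.03 = 3.9025; n = 626.2 and 601.2; SE = 0.0203; 0.06/SE = 2.96; power 84.1%, pooled 83.8% (stated 83%).

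The method therefore matches the plan's own.

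**By sex, 25 v 24 schools.**

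| | DE | n per arm | Difference/SE | Power | Stated |
|---|---|---|---|---|---|
| Girls, climate | 1.915 | 610.3, 585.9 | 3.46 | 93.3% | 93% |
| Boys, climate | 2.000 | 637.5, 612.0 | 3.53 | 94.2% | 88% |
| Girls, bullying, 6 points | 2.3725 | 492.6, 472.9 | 2.62 | 74.7% (pooled 74.2%) | 83% |
| Boys, bullying, 7 points | 2.500 | 510.0, 489.6 | 3.16 | 88.6% (pooled 88.2%) | 82% |

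**Schools that contain each sex.** Section 1.2 selects 63 co-educational, 9 girls-only and 3 boys-only schools, and aims for equal numbers of each type per arm. That gives (63 + 3)/3 = 22 schools per arm with boys and (63 + 9)/3 = 24 with girls. If the TSM school that dropped out was co-educational (the SAP does not say), the contrasts are 22 v 21 and 24 v 23. Keeping the same number per school:
- boys' climate 91.2%, girls' climate 92.3%;
- boys' bullying 84.2% (pooled 83.8%), close to the stated 82%;
- girls' bullying 72.9% (pooled 72.4%), further from the stated 83%.

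**What would produce the stated figures.** With no loss to follow-up and 25 v 25 schools, girls' bullying reaches only 78%. A one-sided 5% test gives girls 83.3%, but would give the whole sample 90%, against 83% stated. At two-sided 5%, 83% in girls needs a prevalence near 14.6% or an ICC near 0.020. Boys' climate power of 88% needs an ICC near 0.031. None of these values is stated.

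**Bullying as a score.** With n = 626.2 and 601.2, SE = 0.0571 SD. The difference detectable with 83% power is (1.960 + 0.954) × 0.0571 = 0.166, about 0.17 SD. This assumes that the ICC of 0.03 carries over to the score.

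**Reported end-line sample** (Figure 1). 4,623 and 5,316 students were analysed in 25 schools each, and 4,475 in 24: about 185, 213 and 186 per school, against 97.75 planned. If girls are 55/115 of these, there are about 88, 102 and 89 girls per school. Girls' bullying power against the 24-school arm is then about 83% (4,623) and 84% (5,316), or 82–83% with 24 v 23 schools.

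**The case against.** The strongest reply is that sex-specific pilot values may lie behind the figures, so that they are correct but poorly documented. That is possible, and it is why the point is put as figures that do not follow from the inputs shown. It does not clear the text, which attributes them to the listed assumptions.

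A reader might infer that all the sex-specific powers are wrong. They are not. Girls' climate reproduces, and boys' bullying is nearly reached once only schools with boys are counted (about 84%, or 82.5% with a t reference on 41 degrees of freedom). The count of schools can also put boys' climate power slightly below girls' (91.2% against 92.3%), but not at 88% against 93%. It depends on how students are spread: if the same boys sit in fewer, larger clusters, boys' bullying power is about 86%.

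A reader might also infer that a null bullying result in girls would be judged against power the trial lacks. The reported sample does not support that: at that size, and with the planned share of girls, power is about 83%.

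Finally, a reader might infer that separate models for boys and girls will lead to a false claim of a gender difference. Objectives 4 and 6 promise stratified results only, and the SAP nowhere says it will compare significance between the sexes. On the endpoint, section 3.1.2 provides logistic models for binary outcomes, so a binary bullying analysis is not excluded; but the SAP neither names bullying as binary nor gives a cut-off.

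**Conclusion.** Two of the four sex-specific powers are wrong as written. Girls' bullying power for 6 points is overstated by about 8 to 11 percentage points (83% stated; 74–75% recomputed, 72–73% with schools containing girls). Boys' climate power is understated by about 3 to 6 points (88% stated; 94% recomputed, 91% with schools containing boys). Only the girls' bullying figure errs in the favourable direction. The bullying endpoint mismatch also stands.

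These results rest on the stated common prevalence, SD and ICCs, equal cluster sizes, 15% loss and a two-sided 5% test. The lower figures also assume equal numbers of each school type per arm and a co-educational TSM dropout. Whole-sample power for the primary outcome is sound. This is an error in a planning statement for secondary analyses, with limited practical effect at the reported sample size.

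**What to change.** In section 1.2, restate the girls' bullying and boys' climate powers from the stated inputs, using the number of schools that contain each sex. Alternatively, give the sex-specific prevalence, SD, ICC and school numbers that produce 83% and 88%. Power may also be restated at the reported end-line size, with the actual numbers of boys and girls.

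For bullying, either name the single binary item as the analysed endpoint in Table 1 and section 3.1.2, or keep the 0–12 score and state power for it (about 83% for 0.17 SD at ICC 0.03).

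An arm-by-gender interaction, reported with its interval beside the sex-specific effects, would be a useful optional addition; it does not correct an error.

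The cost is SAP wording only, with no new data. If the stated common inputs are kept, one planned power becomes less favourable and one more favourable.
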